## 2. Materials and Methods

### 2.1. Study Design and Participants

The current study will have a quasi-experimental design with a control group, which will be target children enrolled in third grade of primary education from 26 schools of the province of Cádiz. The inclusion criteria that will be used will be: children belonging to the selected school, who are in the third grade of primary school, regardless of their age, who have the informed consent signed by their parents or legal guardians, who respond to the questionnaires and who undergo to the anthropometric measurements. The exclusion criteria will be that these requirements are not met.

The total number of study participants will be between 850 and 900 children. The parents of each schoolchild will be part of that same subject (father, mother and child are the same subject of study). The sample will be divided into two groups, the intervention group and the control group. The intervention group will contain around 450 schoolchildren and will be made up of 13 of the 26 school centers which will participate in the study. In this group, pre-intervention measurements will be performed, which will be explained later. A multimodal intervention will be developed, which will also be explained in detail later. Finally, post-intervention measurements will be made, which will be the same as the pre-intervention measurements. The control group will also contain around 450 schoolchildren and will be made up of the others 13 school centers which will participate in the study. It will be made up of the same number of schoolchildren. The difference with respect to the intervention group will be that the control group will not receive any educational intervention. Only the pre- and post-intervention measurements will be taken, to later compare the results with the intervention group and find out if an effect has emerged or not.

The province of Cádiz will be divided into four areas: Campo de Gibraltar (six schools), Jerez-Costa Noroeste (five schools), Sierra de Cádiz (nine schools) and Bahía de Cádiz-La Janda (six schools) (Figure 1). In each area, there will be between 200 and 300 participants and school centers belonging to both the intervention group and the control group. This division will be made to have a sample that is as representative as possible of the entire province of Cádiz.

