Both the selection of schools participating in the study and the assignment of them to the experimental group or control group will be made randomly from the list of public schools of the Cádiz Education Delegation. These randomizations will be carried out taking into account the schools belonging to each of the geographical areas in which the province of Cádiz will be divided, the socioeconomic condition of the population served, which will be determined from the Material Deprivation Index (MDI) of the section of the census in which the school is located [37], and the number of classes or corresponding lines of each center belonging to that age group. Randomization will be carried out in groups by schools, not individually. 

The group of schoolchildren will constitute the first level of analysis, and the schools will be the second level. This target population (children 8–9 years) has been selected due to the need to detect and solve the problem of childhood obesity in early stages to promote healthier lifestyle habits, and thus achieve health benefits that allow correct weight management from childhood until adulthood, and because, at this age, children are very receptive to receiving information that implies changes in habits [23].

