### 2.3. “PREVIENE-CÁDIZ” [CADIZ-PREVENT] Intervention Protocol

The “PREVIENE-CÁDIZ” [CADIZ-PREVENT] intervention (S1) will have a multimodal nature and will be aimed at schoolchildren, their families and schools. The intervention activities/sessions will be implemented by the teachers at the school centers. The research team will train those teachers to implement the program, and parents in a face-to-face session, but not schoolchildren. To achieve this, before implementing the intervention, the management teams and teachers of the intervention group will receive training sessions managed by the CEP (Center for Teacher Education) of Cádiz from the research team. These sessions will last 10 classroom hours and will be aimed at updating knowledge on promoting healthy lifestyle habits (healthy eating, promoting physical activity, reducing sedentary lifestyle, the importance of sleep and promoting health based on resources). Moreover, the sessions will be addressed for the teaching context, and they will show how to use the tools available to implement the intervention. All the information covered will be made available to the teaching staff through the “Moodle” virtual tool that will allow the research team and teaching staff to be in permanent contact to resolve any possible doubts. There will also be chat tools for management teams and research teams.

The intervention will be implemented in three settings: classroom, family and school. See the description of each setting below.

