The dependent variables of our study will be BMI, skinfold thickness of the triceps, waist/hip ratio (as anthropometric variables) and the prevalence of overweight and obesity. As surrogate or intermediate variables we will analyze behaviors related to eating, physical activity and sedentary lifestyle, hours of sleep, knowledge and beliefs about eating and physical activity, as well as the physical condition (IFIS) [44,45] of the children.

In the models, possible covariates related to personal, family, school and environment characteristics will be analyzed. Especially will be analyzed: sex, birth weight, breastfeeding, sociodemographic characteristics, family socioeconomic level, level of physical activity and time of sedentary activities of the parents; behavior, knowledge and beliefs about family food and physical activity, participation of the school in the intervention and level of adherence, participation of the center in other health promotion programs, availability or use of the school canteen and the existence of health assets in the environment.

To determine the efficacy of the different components of the intervention, predictive models will be obtained for each of the outcome variables by backward multiple linear regression, in which all possible components are included and are progressively eliminated from lowest to highest contribution. To analyze the specific contribution of a certain component on a dependent variable, the semi-partial correlations will be obtained; this method allows the effect of the component to be controlled to be subtracted from the predictors being treated. The R^2^ values of the components measure their theoretical contribution and allow establishing a theoretical hierarchy among the components that will be used in the regression by blocks; by changing R^2^ the different contributions of the variables will be seen.

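### Regression on components that every intervention school receives together cannot establish the efficacy of each one; the allocation identifies only the effect of the whole package

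*Protocol article*

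**What the plan says.** Section 2.5 (Statistical Analysis) gives the component analysis its own aim: "To determine the efficacy of the different components of the intervention, predictive models will be obtained for each of the outcome variables". The models are to be built "by backward multiple linear regression, in which all possible components are included and are progressively eliminated from lowest to highest contribution". Semi-partial correlations then isolate the contribution of single components, and the R² values are said to "allow establishing a theoretical hierarchy among the components that will be used in the regression by blocks". The section does not describe this analysis as exploratory or associational.

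Section 2.1 sets out the design. "The sample will be divided into two groups, the intervention group and the control group", with 13 of the 26 schools in each. "Randomization will be carried out in groups by schools, not individually". In contrast to the intervention group, "the control group will not receive any educational intervention".

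Section 2.3 describes a single programme: "The intervention will be implemented in three settings: classroom, family and school". Sections 2.3.1 to 2.3.3 fill it with ten classroom sessions, active recess, a parent workshop, a home workbook, Photovoice and teacher training. No school, class or family is assigned only part of it.

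**The concern.** An efficacy claim for a component needs a comparison between children allocated to it and children not allocated to it, with the other components balanced. This design provides that comparison for the package and for nothing smaller. A regression that ranks components must therefore use differences that arose after allocation: which families attended or completed the workbook, and which teachers delivered more. Those differences follow motivation and circumstances as well as any effect of the component.

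If the plan is followed as written, the trial would report some components as efficacious and others as dispensable, when the ordering may show who took part rather than what worked.

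**Working it through.** **1. The plan's own figure.** Section 2.2 gives 410 children per group for 35% against 26%, 95% confidence and 80% power. Two-sided, with pooled variance and mean proportion 0.305:

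n = [1.960·√(2·0.305·0.695) + 0.842·√(0.35·0.65 + 0.26·0.74)]² / 0.09² = [1.276 + 0.545]² / 0.0081 ≈ 410.

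The figure reproduces. It sizes the package against control. Section 2.2 gives no size for any component, and the present point does not depend on 410.

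**2. Components as assigned.** Let A = 1 in intervention schools and 0 in control schools. Every component indicator C_k then equals A, and

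y = α + Σ β_k·C_k = α + (Σ β_k)·A.

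Only α and the sum Σ β_k can be estimated. A check with 26 schools, four illustrative components and an intercept gave 5 columns and rank 2. The article gives no count of components, but the rank stays at 2 for any number. Backward elimination on such columns has nothing to choose between.

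**3. Components as taken up.** The remaining variation is in uptake and delivery, and three features of the plan bear on it.

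- Section 2.6 schedules the school calendar so that every school delivers every session. The squared semi-partial correlation of a component is β_k²·Var(C_k given the others)/Var(y). For yes/no uptake in a proportion p of children, the variance of C_k is p(1−p), which is zero at p = 1. A component delivered uniformly therefore ranks last whatever its effect.
- Section 2.3.2 gives families who miss the workshop its audiovisual material and a summary document. Attendance is thus not a contrast between having and not having the content.
- Section 2.4.10 treats child and caregiver adherence partly as changed behaviour at home. Section 2.5 lists such behaviours as intermediate variables, so adherence in that sense is a result of the programme and not a measure of exposure to it.

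**4. Illustration of confounded uptake.** All inputs are assumptions:

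- 13 schools × 33 children = 429 children, and no component has any effect.
- Unmeasured family engagement raises workshop attendance (yes/no) and workbook completion (continuous), with coefficient 0.5 for each.
- Classroom dose varies by school and is unrelated to engagement.
- Components are removed at p > 0.05. There are no covariates, no school effect on the outcome, and 1,000 runs per row.

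| Engagement lowers the outcome by (residual SD per SD) | Classroom dose retained | Workshop retained | Workbook retained |
|---|---|---|---|
| 0 | 5.2% | 5.0% | 5.1% |
| 0.1 | 5.5% | 9.9% | 12.6% |
| 0.2 | 5.3% | 24.4% | 42.4% |
| 0.3 | 4.5% | 46.4% | 69.1% |

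The Monte Carlo standard error is at most √(0.25/1000) = 1.6 percentage points. The two family components appear to outperform the classroom sessions although nothing works. The workbook also appears to outperform the workshop. Both depend on engagement with the same coefficient, so that gap comes only from coding one as yes/no and the other as a continuous score.

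**The case against.** The best defence has three parts.

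*The wording is softer than it looks.* The section speaks of predictive models and a theoretical ranking, and elsewhere treats regression as a measure of association. That is true, but the sentence that sets the purpose says efficacy, and nothing qualifies it.

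*Components may mean something else.* They could be content domains (diet, activity, sedentary time, sleep), which are measured in both arms. The rank argument in step 2 would then not apply. These would still be behaviours observed after allocation and not themselves allocated, so a causal ranking remains unsupported. An article may leave the definition of the variables to a fuller plan, and its absence is not criticised here.

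*Confounding is partly handled.* Section 2.5 lists family socioeconomic level, parental activity, and family behaviour and beliefs as possible covariates. A reader should not infer that socioeconomic level is ignored. Adjustment could bring the simulated rates down, but it does not remove motivation that was not measured.

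Stronger readings are tempting, and the document does not support them:

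- *School clustering is ignored, and prevalence gets a linear model.* The component paragraph names only linear regression, but the same section promises multilevel modelling and provides for logistic regression. It does not say whether these carry over.
- *Delivery varies over no more than 13 units.* Teachers set the timing of sessions, and Section 2.5 includes a classroom level, so delivery can vary within schools.
- *The R² ranking will decide how the programme is adapted.* The Conclusions speak of factors that influence effectiveness and of characteristics of the population. They do not mention the ranking.
- *A definite number of false positives can be stated.* The article gives neither the number of components nor a removal threshold.

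**Conclusion.** The plan is wrong as written on this point. The allocation identifies one effect, that of the package against no intervention. The component analysis can describe associations with uptake or delivery but cannot determine efficacy, and an R² ranking also reflects how much each component's uptake happens to vary.

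For components as assigned, this follows from the two-arm design and needs no assumption about numbers. For components as taken up, it rests on uptake not being randomised, which the document makes clear. The size of the resulting bias is unknown. The simulated retention rates show the mechanism under assumed values and are back at 5% when engagement does not affect the outcome.

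The main comparison of the arms and its sample size do not depend on this analysis.

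**What to change.** 1. State in Section 2.5 that the trial estimates the effect of the package only.
2. Relabel the component analysis as exploratory and associational, and remove the word efficacy from its aim.
3. Do not use backward elimination, semi-partial correlations or the R² hierarchy to rank components.
4. Report instead, for each outcome, one model with a pre-listed set of uptake variables, all retained. Carry over the school grouping already promised in Section 2.5, include the baseline outcome and the listed covariates, and use a logistic form for prevalence.
5. Define uptake as participation or delivery (sessions given, attendance, workbook completed), separately from behaviour change at home. Table 3 names the World Cafe in four intervention schools and the teacher and management questionnaires as its adherence sources. Family-level uptake would have to come from elsewhere, for example the teachers' workbook review in Section 2.3.3, or be left out.

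**Cost.** Allocation, sample size and the main comparison stay as they are. One secondary analysis is re-specified, and some uptake recording may need to be made explicit. The trial gives up a ranking of components that its design cannot support. Component effects with a causal reading would need components to be allocated separately, as in a factorial design, which would be a different trial.

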### 2.6. Timeline of the Intervention

With the intention of covering the proposed objectives, the intervention will be conceived as a gradual process in which three phases will be able to be distinguished fundamentally: (I) preparation phase, (II) implementation phase and (III) evaluation and dissemination phase.

Phase I will essentially cover the first year of the project. It will include activities such as the search and updated review of the scientific literature, preparation of the necessary material to carry out the evaluations and the intervention (questionnaires, educational program, booklets), consensus meetings between the research team, recruitment and meetings with the management teams and/or teachers from the centers participating in the study, recruitment of participating teachers and agreements on the monitoring system during the intervention, design and implementation of teacher training and design of workshops for families.

Phase II, which will be the implementation phase, will cover the second year of the study. It will include activities such as conducting pre and post intervention evaluations, implementation of the multimodal intervention, realization of workshops for families, creating databases and entering data. In addition, it will include activities such as the identification of resources/assets for health related to healthy eating and physical activity in the environment of each school, through the Photovoice technique. In turn, it will include the implementation of the World Cafe technique, which will be used to describe the perception of the participants of the intervention (schoolchildren, teachers and parents). Finally, it will include the identification of the current prevalence of childhood overweight and obesity in the province of Cádiz.

All schools will have the same time to implement the intervention (6 months). Within these 6 months, each school will have to combine its usual activities with the implementation of the educational program. To guarantee that all the schools carry out all the sessions, the research team will schedule the school calendar with the teachers and management teams of the participating centers in the teacher training workshops that will be carried out in phase I. The research team will provide to the schools all the necessary resources to implement the educational program.

Phase III, which corresponds to the evaluation and dissemination phase, will basically cover the third and final year of the study. It will include activities such as the statistical analysis of the data and disseminating results. The results will be disseminated both to the scientific community (through scientific papers, congresses, conferences, etc.) and to the participating schools (through a report in which the main results of the study will be specified). In addition, it is also intended to disseminate the results to society in general, so that the relevant authorities become aware of the problem and, if it is possible the intervention is implemented (with all the relevant modifications) in as many schools as possible.

## 3. Discussion

“PREVIENE-CÁDIZ” [CADIZ-PREVENT] intervention is based on the scientific literature on strategies to reduce childhood overweight and obesity. The design of the most effective interventions for the prevention of childhood obesity must include an education program carried out in the classroom and at home, where children and parents work aspects such as the practice of regular physical activity [53], recreational activities [54], extracurricular sports [35], reduced screen time, reduced fat consumption, increased fruit and vegetable servings and decreased consumption of carbonated beverages [54], in order to improve the behavior of children and parents and get them to acquire healthier lifestyle habits [29].

According to a Cochrane Review [29], most interventions take place within the 6–12 year range. Solid evidence has been found regarding the benefits which can be obtained within those ages [29]. This result is consistent with a later review [29] which concludes that those interventions combining physical activity and diet were those which yielded the best results both in their family settings and in school. Taking this into account, it can be very interesting to delve deeper into this age range, focusing on third grade of Spanish Primary Education due to the maturity of the students to be able to fill in questionnaires and to understand the intervention. Due to the fact that this intervention will take place through sessions included in their ordinary curriculum, it is necessary to pick a subject to develop such material and to implement it on the same level in all schools, considering that such school year is the best one to do that. In addition, this age has been chosen by other authors for different interventions on health promotion [25,55].

Among the strengths of this project, we highlight that a multimodal intervention will be carried out incorporating the main agents responsible for education (school and family) on a representative sample of boys and girls aged 8–9 years from the province of Cádiz. In addition, the multidisciplinary composition of the research team with more than 10 different disciplines and the continuous feedback and workshops (seminars) between the research team and the teachers will be strengths of the PREVIENE-CÁDIZ [CADIZ-PREVENT] project.

Regarding sustainability, it is worth mentioning that the initiative could be extended without the need for considerable additional resources. The fact that the educational sessions are implemented by the teachers enables an easier continuity of the intervention. 

As a limitation, getting all the schools in the intervention group to carry out the ten sessions on the planned schedule will be a challenge for the project. For this limitation, a contingency plan is contemplated whereby, through the teacher training courses developed by the research team in the CEP of Cádiz, a section will be included to organize the scholar calendar with the management teams and teachers. This will ensure that all schools commit to implementing the intervention at the same time, and it is expected that this will favor the implementation of the sessions.

In another vein, not measuring the physical condition of schoolchildren and family members objectively, but doing so subjectively using the self-report questionnaire of perceived physical condition (IFIS), could be a limitation. However, due to the complexity of bringing together schoolchildren, and especially their families to perform a series of physical tests, a decision has been made to use the IFIS scale, which has previously been validated and used in this population group [44,45].

## 4. Conclusions

This study will enable the evaluation of the effectiveness of an educational multimodal intervention at the individual, school and family levels, focused on the acquisition of healthier lifestyle habits with regard to diet, increased levels of physical activity, reduced sedentary lifestyle and improved sleep to prevent overweight and obesity in a representative sample of schoolchildren from 8 to 9 years old in the province of Cádiz. Once the evaluation has been carried out, the weaknesses and strengths of the educational program with respect to the population of the third year of primary education as a target group will be able to be identified, and therefore, timely decisions will be able to be made to adapt, modify and improve the educational intervention.

The results of this project will allow for the creation of well-adapted educational programs for this child population, which will be able to serve as a reference for the implementation of similar programs in other locations. Once the factors that will influence the possible effectiveness of the educational intervention have been determined, its implementation strategy (focused, selective or adapted implementation) will be able to be improved according to the personal, behavioral, family, and contextual characteristics of the relevant target population.

